#### Outcomes

**Table Taba:** 

Assessments	Screening	Baseline	8 weeks	52 weeks
*Vestibular testing*				
Saccule	x		x	x
Utricle	x		x	x
Semicircular canals	x		x	x
*Falls*		x	x	x
*Fall risk factors*				
Medications		x	x	x
Strength		x	x	x
Other sensory (vision, proprioception)		x	x	x
*Balance testing*				
Berg Balance Scale		x	x	x
Timed Up and Go		x	x	x
*Cognitive testing — spatial*				
Clock drawing test		x	x	x
Card Rotations test		x	x	x
Money Road Map test		x	x	x
Triangle completion task		x	x	x
*Cognitive testing — other domains*				
RBANS		x	x	x
MMSE		x	x	x
Trail Making Test		x	x	x
COWAT		x	x	x

The endpoint for the current proposal is an incident fall, defined as a participant “coming to rest inadvertently on the ground or other lower level” [72]. We will ascertain fall events using monthly calendars, which are considered the gold standard of prospective fall measurement. Patients and caregivers will be given 12 self-addressed stamped envelopes to return each monthly calendar. If we do not receive a calendar within 2 weeks of the expected receipt date, we will call the patient by telephone. For any fall that is reported, we will collect standardized information including any injuries that occurred, per the procedures developed for the STRIDE trial [73]. Additionally, given that multiple risk factors have been shown to contribute to falls in AD patients, we will also measure other known fall risk factors, including history of falls, medications (number of CNS-active medications and anticholinergic burden), strength (using hand dynamometer), and other sensory factors (vision assessed using Snellen visual acuity and Pelli Contrast Sensitivity charts; proprioception assessed using Romberg test), based on published procedures in AD patients [74–80].

In order to measure outcomes related to balance, we have chosen the Berg Balance Scale (BBS) and the Timed Up and Go (TUG) test because both tests have been well-validated in AD patients, are easy to administer (~5–10 min for both tests), and have shown excellent test-retest reliability among patients with mild-moderate AD (intra-class correlation coefficient for both the BBS and TUG ≥ 0.9) [81–85]. Studies showed that patients with mild-moderate AD were able to complete all of the balance tests, although some participants required additional cueing to remember steps in the test instructions. The BBS assesses the ability to maintain balance during a set of 14 simple, everyday tasks. Each item is graded on a 5-point scale, ranging from zero (patient unable to perform task) to four (patient can independently complete the task for the full duration), for a total possible score of 56. Additionally, given the increased sensitivity of quantitative postural testing in detecting mild balance impairment in AD patients (18), we will measure center-of-mass sway during standing tasks in the BBS using the BalanSens™ posturography system per established procedures in our laboratory [86]. The TUG test is a widely used clinical test that incorporates a series of tasks critical for independent mobility: standing up from a seated position, walking 3 meters, turning back around, walking, stopping, and sitting down [87]. Subjects are instructed to perform the task as quickly as is safely possible, and the time taken from bottom off the seat to bottom back on the seat is measured using a stopwatch. In this study, the mean time to completion of two trials of the TUG will be recorded.

Measures to assess cognitive outcomes will include assessments of spatial and nonspatial cognitive function. We selected the clock drawing test, the Card Rotations test, the Money Road Map test, and the triangle-completion task as spatial cognitive measures that assess various aspects of spatial cognition (including mental rotation, spatial memory, and spatial navigation). These tests can be given to patients with a wide range of cognitive deficits and altogether take ~10–15 min to administer. The clock drawing test requires patients to draw an analog clock and draw the hands to depict a specified time [88]. The clock drawing test assesses conceptually guided constructional praxis and also requires executive skills. Drawings are scored based on accuracy, with consideration of spacing of the numerals within the clock face, completeness and correctness of numerals, and hand placement. In the Card Rotations test, subjects are shown a reference shape, followed by a series of similar objects that are variously rotated [89]. Subjects are asked to mentally rotate the objects to determine whether they are identical to or mirror images of the reference shape. The score is the number of correct responses minus the number of incorrect responses completed within 3 min. In our prior work, we found that performance on this test was strongly correlated with vestibular function in healthy older adults [61]. The Money Road Map test involves a map with a path that has 32 corners. Patients are asked to imagine themselves walking along a path and indicate when they get to a corner if they are to turn right or left to stay on the path [90]. This test assesses the ability to make egocentric mental rotations (i.e., in reference to one’s own point of view). The test is scored based on the number of errors made (range 0–32). Patients with AD have been shown to perform worse on this test compared to control subjects, and the range of performance on this test has been shown to vary widely among AD patients [91]. Moreover, we recently reported that AD patients with vestibular loss had significantly poorer performance on this test relative to AD patients with intact vestibular function [92]. The triangle-completion task (TCT) measures dynamic spatial navigation. Patients are moved along two limbs of a triangle wearing a blindfold and are asked to turn and return to the perceived origin of the triangle on their own. This test has been extensively used in older adults (including in the Baltimore Longitudinal Study of Aging) as well as in patients with vestibular disorders [93–95]. We will also explore the effect of VT vs. active control on nonspatial cognitive tests, measured with the Repeatable Battery for Neuropsychological Status (RBANS), focusing on the immediate and delayed memory, language, and attention domains [96]. We will also administer the Trail Making Test (TMT) and the Controlled Oral Word Association Test (COWAT) as measures of executive function and the MMSE as a global measure of cognitive function [97–99].

We propose to evaluate fall events over a 1-year follow-up period given that prior studies demonstrating feasibility of using VT have shown benefit in reducing fall rates and improving balance outcomes up to 12 months following VT [36]. Of note, we will be collecting monthly falls data, such that if there is an initial difference in fall rates between the 2 groups that starts to narrow during the follow-up period, we can consider including “booster” VT sessions in subsequent trials. Additionally, we will evaluate short-term balance and cognitive outcomes at the completion of the 8-week course of VT. Prior studies of VT in patients with chronic vestibular loss have shown improvements in balance and gait performance when assessed from 8–16 weeks after baseline following an 8-week course of VT [100–102]. In order to explore the longer-term “disease-modifying” effects of VT in AD patients, we will also secondarily assess balance and cognitive outcomes at 1 year. Furthermore, we will consider whether balance and cognitive function during the follow-up period mediate the association between VT and 1-year incidence of falls. We will also assess vestibular function at 8 weeks (short term) and 52 weeks (long term) given that further deterioration of the vestibular apparatus may influence VT outcomes.

### Sample size

As mentioned previously, we will enroll 100 AD patients with vestibular loss who will be randomized 1:1 into the control and intervention arms of the trial.

We note that the goal of this pilot trial is to determine design feasibility and preliminary efficacy, i.e., estimate effect size, of VT on 1-year falls incidence. As such, we are choosing a convenience sample of 100 patients, to balance the competing considerations of enrolling a sufficient sample size to overcome heterogeneity in fall rates, though not committing undue effort and resources to an intervention that still requires higher level of evidence before conducting a definitive phase 3 trial. We used the recurrent event data simulation algorithm developed by Jahn-Eimermacher et al. [103] to estimate the power associated with enrolling a convenience sample of 100 participants. We made the following assumptions based on the literature and prior experience: (1) 70% of untreated individuals will experience at least 1 fall during the year of follow-up; (2) those who fall experience an average of 3 falls per year [104]; (3) the rate for loss-to-follow-up over 2 years is 20% (a conservative estimate based on prior studies in the JHMATC, with losses to follow-up due to patient relocation, institutionalization, and death), and the dropout follows a uniform distribution over the 2-year interval. The effect sizes (hazard ratios) of 0.4, 0.5, and 0.6 (associated with enrolling 100 participants) correlate with powers of 95%, 80%, and 56%, respectively. As a frame of reference, in cognitively intact older adults, multifactorial fall risk reduction interventions have reduced fall rates by ~40–50% [105, 106], and single interventions such as cataract surgery have reduced fall risk by 30–40% [107]. Additionally, we tested the effect on our statistical power of adding the other baseline covariates to adjusted models. Compared to the crude analysis, we will gain power by including confounders that have a meaningful association with falls (e.g., assuming that the combined confounders increase the odds of falls by ~threefold). We will balance the study arms on age and baseline MMSE using dynamic minimization software developed by the study statistician [108].

### Statistical methods

With regard to the primary objective of determining the feasibility of this study design, descriptive statistics on the patient population recruited will be summarized to understand how effective our recruitment and attrition strategies have been. Continuous variables (such as age) will be summarized as means and associated standard deviations if normally distributed or medians and associated ranges for skewed data. Categorical data will be summarized as counts and percentages.

With regard to the falls-related data, we will treat incident fall events as recurrent events such that the sequence of times of the recurrent event (i.e., repeated falls) constitutes a simple point process recorded continuously over the 1-year follow-up period. We will model the intensity of the recurrent events using the Andersen-Gill (AG) model [109], which generalizes the Cox proportional hazard model for counting processes. This model will also be adjusted for baseline covariates including age, sex, hearing, disease duration, fall risk factors, balance, and global cognition. In secondary analyses, we will include interaction terms between these covariates and treatment assignment to assess possible predictors of treatment response. For example, the coefficient for the interaction between female sex and VT would be the difference in treatment effect between females and males.

With regard to balance, to evaluate whether participants improve after therapy, we will fit a longitudinal random effects model with a random intercept such that E[*y*_ij_] = *β*_0_ + *β*1 visit + *β*_2_ VT + *β*_3_ VT × visit, where *y*_ij_ is the outcome (BBS or TUG) for the *i*th participant at the *j*th visit (either baseline (0) or post treatment (1)), *β*_0_ is the fitted mean outcome at baseline for individuals in the active control arm, *β*_1_ is the fitted change in outcome comparing post- to pre-treatment visits among those in the active control arm, *β*_2_ is the between-arm difference at baseline (assumed to be 0), *β*_3_ is the between-arm difference in change in outcome over time, and can be interpreted as the treatment effect. The regression model will also be adjusted for baseline covariates including age, sex, hearing, disease duration, balance, cognition, and fall risk factors. In secondary analyses, we will include interaction terms between these covariates and visit × VT to assess possible predictors of treatment response.

We will also explore whether changes in balance and/or cognition during the follow-up period account for (i.e., mediate) the impact of VT on falls. The models described in aim 2 will be similarly applied here to evaluate change in cognitive function following VT. If there is an effect VT on cognitive function, we will assess the relationship between VT and primary outcomes after adjusting change in cognition. Secondarily, we will fit similar models to the nonspatial cognitive outcomes. If there is appreciable improvement in nonspatial cognitive outcomes, we will regress nonspatial change scores on spatial change scores (adjusting for baseline scores) to determine if gains in nonspatial domains are correlated with spatial gains.

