**Methods:**

The proposed pilot clinical trial will be a parallel-group randomized controlled trial. Patients with a diagnosis of mild-moderate AD, age ≥ 60, and the presence of a caregiver will be recruited from the Johns Hopkins Memory and Alzheimer’s Treatment Center. Eligible patients will be offered vestibular testing. Patients with vestibular loss will be offered participation in the VT trial. One-hundred AD patients with vestibular loss will be enrolled and randomized 1:1 into the control and intervention arms of the trial. All patients will undergo baseline balance and cognitive assessment, followed by 8 weeks of active control therapy or VT, consisting of ~25-min office sessions with a vestibular therapist. Patients will be tracked for falls and undergo follow-up balance and cognitive assessment at 8 and 52 weeks (1 year) to assess the potential short-term and longer-term effects, respectively, of VT on balance and cognition. The main outcomes of this trial are falls, balance (using the Berg Balance Scale and the Timed Up and Go test), and cognition (using the clock drawing test, the Card Rotations test, the Money Road Map test, and the triangle completion task).

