
The primary aim of this feasibility trial is to evaluate the trial design with regard to aspects such as method of recruitment, attrition rate, and assessing choice of primary outcomes for the main trial. This will be accomplished through the study of three secondary aims. The first is regarding falls. We will evaluate the feasibility of using VT to reduce falls in patients with AD. We hypothesize that VT will have preliminary efficacy in reducing 1-year incident fall rates relative to an active control intervention in a convenience sample of 100 patients with mild-moderate AD. The second is regarding balance. We will evaluate the feasibility of using VT in improving balance in patients with AD. We hypothesize that VT will have preliminary efficacy in improving balance as measured by the Berg Balance Scale (BBS) and the Timed Up and Go (TUG), relative to the active control intervention, at 8 weeks and 1-year after randomization. The third is regarding spatial cognition. We will evaluate the feasibility of using VT in improving spatial cognition in patients with AD. We hypothesize that VT will have preliminary efficacy in improving spatial cognition as measured by the Money Road Map, the Card Rotations, and the clock drawing tests, relative to the active control at 8 weeks and 1 year.

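### The balance and cognition model has a 0/1 visit term and one treatment effect, so as written it cannot give both the 8-week and the 1-year effects that are hypothesized

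*Protocol article*

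**What the plan says.** **Hypotheses.** The aims at the end of the Background expect better balance with VT "relative to the active control intervention, at 8 weeks and 1-year after randomization", and better spatial cognition "relative to the active control at 8 weeks and 1 year". The abstract gives the two follow-ups different jobs: "to assess the potential short-term and longer-term effects, respectively, of VT on balance and cognition".

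**Schedule.** The assessment table under Outcomes has the columns "Assessments Screening Baseline 8 weeks 52 weeks". BBS, TUG and every cognitive test are marked at baseline and at both follow-ups. The text under Outcomes places the short-term assessment at the end of the 8-week course and ranks the later one below it: "we will also secondarily assess balance and cognitive outcomes at 1 year".

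**Model.** Statistical methods writes the expected outcome as β0 + β1 visit + β2 VT + β3 VT × visit, with a random intercept. The visit is "either baseline (0) or post treatment (1". The coefficient β1 "is the fitted change in outcome comparing post- to pre-treatment visits among those in the active control arm", and β3 "is the between-arm difference in change in outcome over time, and can be interpreted as the treatment effect". The paragraph after it applies this model to cognition as well.

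**The concern.** The hypotheses ask two questions of each outcome: is there a benefit when therapy ends, and is there one at 1 year? The model has room for one answer. The text does not say which follow-up is coded 1, whether both are, or whether the model is fitted more than once.

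At stake is whether a benefit that fades can be told from one that lasts. The Outcomes section presents the 1-year assessment as the way to explore longer-term effects, so a single undifferentiated coefficient would leave that question unanswered or mixed with the short-term one.

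**Working it through.** The protocol gives no SD, effect size or power for balance or cognition; its power figures concern falls. There is therefore no stated figure to reproduce, and the check is what the written model can identify.

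**Counting parameters.** Two arms at three visits have 2 × 3 = 6 means. The written model has 4 mean parameters (β0 to β3), and only β3 is a treatment effect. Two visit-specific effects need the 6-parameter model or two separate fits.

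**Inputs from the protocol.**
- 100 patients randomized 1:1, so 50 per arm.
- Visits at baseline, 8 and 52 weeks.
- Loss to follow-up of 20% over 2 years, uniform (Sample size), which gives 20% × 1/2 = 10% by 1 year.

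**Assumed inputs.**
- True effects (week 8, week 52) of (4, 0), (3, 1), (2, 2) and (0, 4) points.
- Within-patient correlation of 0.5 and 0.9.
- Share seen at week 52 of 100%, 90% and 80%, with data missing at random with respect to outcome.

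**Reading 1: both follow-ups coded 1.** The expected generalized least squares estimate is (Σ X′V⁻¹X)⁻¹ Σ X′V⁻¹E[y], where V is the random-intercept covariance. It has the form β3 = w·d8 + (1 − w)·d52, where d8 and d52 are the true effects. With complete data w = 1/2, so β3 = (d8 + d52)/2.

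| True (d8, d52) | 100% seen at week 52 | 90% seen | 80% seen |
|---|---|---|---|
| (4, 0) | 2.00 | 2.14 to 2.15 | 2.29 to 2.31 |
| (3, 1) | 2.00 | 2.07 to 2.08 | 2.14 to 2.16 |
| (2, 2) | 2.00 | 2.00 | 2.00 |
| (0, 4) | 2.00 | 1.85 to 1.86 | 1.69 to 1.71 |

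Ranges run over the two correlations. With complete data, all four patterns give the same β3. As week-52 data go missing, the average shifts toward the week-8 effect: at 90% seen, w is 2.14/4 to 2.15/4, about 0.54. The quantity being estimated then depends on the dropout rate.

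**Reading 2: only week 8 coded 1.** β3 is the 8-week effect. The week-52 data do not enter, and the 1-year hypotheses have no model.

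**Reading 3: fitted twice, each follow-up against baseline.** Each β3 is then the effect at its own visit. The article does not say that this is done.

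**With visit as a three-level factor.** The same calculation returns every assumed pair exactly: (4, 0), (3, 1), (2, 2) and (0, 4).

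**The case against.** The best defence is that the equation is plainly a two-visit model. The Outcomes section makes the end of the 8-week course the main short-term assessment and 1 year secondary, and the abstract gives the two visits different purposes. A sympathetic reader would take post treatment to mean week 8 and expect the same form to be used again for week 52. An article may also leave such detail to the full protocol or SAP.

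Much of this stands. Two separate fits would recover both effects, at little cost in precision. With 50 per arm, equal within-patient correlation of 0.5 to 0.9, known covariance and dropout unrelated to outcome (all but the arm size assumed), leaving out week 8 inflates the standard error of the 52-week contrast by 0.4% to 1.1% with 10% missing and by 0.9% to 2.2% with 20% missing.

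What does not stand is that this is only missing detail. The article fixes the equation, the coding and the meaning of β3, and that choice does not match its own hypotheses and schedule. A plan that follows it literally inherits the mismatch.

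A reader might go further and infer that the trial will report a fading benefit at half its size. The documents do not support that: it happens only if both follow-ups are coded 1, and nothing says they are. Nor does the point need any assumption about decline over the year. Deterioration would lower BBS but raise TUG times and Money Road Map errors, so no single direction applies.

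**Conclusion.** The point holds for the single model as written: it cannot deliver both the 8-week and the 1-year effect for balance or, by extension, for cognition. Either β3 averages the two, or the 1-year effect is not estimated. The structural conclusion rests on the parameter count and needs no assumed values. The numerical illustration (an effect of 4 then 0 looking like a constant 2) rests on assumed effects and complete data, and applies only to the reading in which both follow-ups are coded 1.

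It would be too strong to say that the protocol's approach cannot be made to answer its hypotheses. The same equation fitted once per follow-up would do so, if that were stated. The consequence is confined to the balance and cognition analyses, which serve secondary aims. The Andersen-Gill analysis of falls does not use this model, and the feasibility aim is summarized descriptively.

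**What to change.** Replace the 0/1 visit term with a three-level factor (baseline, week 8, week 52), and include separate VT-by-week-8 and VT-by-week-52 terms in one model that uses all visits. Report both contrasts with 95% CIs, week 8 as the main one and week 52 as the secondary one, following the ranking under Outcomes. State that the same specification applies to the cognitive outcomes.

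An acceptable minimum is one sentence saying that the 0/1 model is fitted separately for baseline with week 8 and baseline with week 52. An unstructured within-patient covariance is optional; it is not needed to separate the two effects.

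The cost is a change of wording and two more mean parameters (six instead of four). No extra patients, visits or data are needed.

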
Vestibular therapy (VT) is the mainstay of treatment for vestibular loss, supported by substantial evidence [35]. A recent Cochrane review concluded that there is moderate to strong evidence from high-quality randomized controlled trials that VT improves objective measures of balance (e.g., posturography), improves daily functioning, and reduces symptoms in individuals with vestibular loss [36]. In fact, a number of studies have shown that VT reduces the rate of falls ~20-40% [37–41], in both younger and older adults [42–44]. VT consists of a series of exercises designed to foster compensation for vestibular loss. Vestibular compensation occurs via 3 primary mechanisms: adaptation, substitution, and habituation [45]. With adaptation to vestibular loss, the central nervous system increases its responses to residual intact peripheral vestibular sensors [46]. With substitution for vestibular loss, other mechanisms (e.g., neck muscle proprioceptors) are recruited to replace vestibular contributions to the VOR and VSR [47–49]. With habituation, repeated exposure to provocative stimuli (e.g., fast movement such as running) over time results in a reduction of undesirable symptoms such as dizziness and imbalance [50]. VT is thus known to hasten and strengthen the mechanisms of adaptation, substitution, and habituation in order to improve balance and reduce fall risk in individuals with vestibular loss. Vestibular impairment is also associated with poorer spatial cognitive skills and potentially contributes to a “spatial” subtype of Alzheimer’s disease, characterized by wandering and falls [51]. Thus, VT may also help prevent or mitigate spatial cognitive decline as well. In fact, vestibular dysfunction is also correlated to cognitive impairments in nonspatial cognitive domains including problems in concentration, short-term memory, reading abilities, or executive functions (although it is not clear how VT targets spatial cognition versus other domains of cognitive function) [52]. Despite its potential benefits, VT is typically not offered to AD patients; in surveying our own clinical data, of the 1907 patients seen in the Johns Hopkins Memory and Alzheimer’s Treatment Center in 2018, < 1% (only 5 patients) were referred for vestibular therapy. This may be the case for a number of reasons, including the following: (1) infrequent assessment and diagnosis of vestibular impairment in AD clinical practice and (2) unclear benefit of VT in AD patients (although the benefit of VT on balance function and falls among cognitively intact older adults with vestibular impairment is well-established). As noted previously, vestibular loss in patients with AD is more common and more severe than in healthy older adults [34], and thus, the potential benefit of VT in AD patients may be even greater. Prior studies have shown that even patients with fairly severe AD are capable of motor learning and can improve their motor function following physical therapy [53–57]. Thus, we propose to systematically investigate whether VT can reduce falls and improve balance and spatial cognitive function in patients with AD. Our broader objective is to develop the evidence base needed to increase awareness of vestibular impairment in AD patients and drive use of an existing, potentially beneficial therapy in a patient population whose high level of vestibular deficits is currently going unaddressed.

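### The exploratory test of whether spatial cognition mediates the effect of VT on falls adjusts for change in cognition without naming the baseline score of the same spatial test

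*Protocol article*

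**What the plan says.** All of this is in the protocol article, mainly under Statistical methods.

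- The mediation question is "whether changes in balance and/or cognition during the follow-up period account for (i.e., mediate) the impact of VT on falls".
- For cognition, if VT shows an effect on it, "we will assess the relationship between VT and primary outcomes after adjusting change in cognition". I read the outcome here as falls, because the paragraph opens with falls.
- The falls model is an Andersen-Gill model: "This model will also be adjusted for baseline covariates including age, sex, hearing, disease duration, fall risk factors, balance, and global cognition".
- Under Outcomes, global cognition is a separate instrument from the four spatial tests: "the MMSE as a global measure of cognitive function". The fall risk factors listed there (fall history, medications, strength, vision, proprioception) contain no spatial score.
- For a neighbouring analysis the baseline is named: "we will regress nonspatial change scores on spatial change scores (adjusting for baseline scores").
- The assessment table under Outcomes schedules all four spatial tests at baseline, 8 weeks and 52 weeks.

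So the balance mediator has its own baseline in the named covariates of the falls model. The spatial-cognition mediator does not.

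**The concern.** A change score is the follow-up score minus the baseline score, so it usually correlates negatively with baseline. If a patient's fall rate depends on how good spatial function is at follow-up, regressing falls on change alone mixes that dependence with the patient's starting point, and the slope is distorted. Baseline MMSE stands in for the missing baseline only as far as it correlates with the spatial test.

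The protocol gives some reason to think that level matters. The Background links vestibular impairment to poorer spatial skills and to a spatial subtype of Alzheimer's disease "characterized by wandering and falls".

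At stake is the exploratory answer on mechanism. In the diluted case, the VT hazard ratio moves too little when cognition is added. A real cognitive pathway would then look weaker than it is, and the direct effect of VT stronger.

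**Working it through.** **1. The plan's own figure.** The protocol gives no number for the mediation analysis. Its only related figure is the power under Sample size. I reproduced it to confirm the fall process used below.

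- Inputs from Sample size: "70% of untreated individuals will experience at least 1 fall during the year of follow-up"; 3 falls per year among fallers; 50 per arm. The control mean is 0.7 × 3 = 2.1 falls.
- Gamma frailty variance θ from (1 + 2.1θ)^(−1/θ) = 0.30 gives θ = 0.852.
- Var(log HR) = [(1/μ0 + θ) + (1/μ1 + θ)]/50, with two-sided α = 0.05 (assumed; not stated).
- At HR 0.5: (0.476 + 0.852 + 0.952 + 0.852)/50 = 0.0626, so SE = 0.250. Then 0.693/0.250 − 1.96 = 0.81, which gives power of 79.1%.
- HR 0.4 and 0.6 give 94.2% and 55.4%. The stated values are 95%, 80% and 56%, so they are reproduced.

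**2. Slope on change without its baseline.** Let M0 and M1 be the baseline and follow-up spatial scores, ρ = corr(M0, M1) and r = corr(M0, MMSE). The log fall rate contains b·M1 + c·M0. Neither ρ, r, c/b nor the SDs are in the protocol; all are assumptions.

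Take equal SDs (set to 1) and c = 0, so that falls depend on the follow-up level. With MMSE partialled out, the residual variance of M0 is 1 − r², and M1 = ρM0 + e with var(e) = 1 − ρ². Then:

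- cov(M1, change) = (1−ρ)(1 + ρr²)
- var(change) = (1−ρ)[2 − r²(1−ρ)]
- share of b retained = (1 + ρr²) / [2 − r²(1−ρ)]

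At r = 0 this is 1/2 for any ρ. At r = 0.6, ρ = 0.7 it is (1 + 0.252)/(2 − 0.108) = 1.252/1.892 = 0.66, a loss of 34%. Over ρ = 0.5 to 0.9:

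| r (spatial with MMSE) | share lost |
|---|---|
| 0 | 50% |
| 0.3 | about 46% |
| 0.5 | 38-40% |
| 0.6 | 33-35% |
| 0.8 | 19-21% |

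A Poisson-gamma simulation (400,000 patients, ρ = 0.7) gave 49%, 38% and 34% lost at r = 0, 0.5 and 0.6. With the test's own baseline added, the loss was −2% to +1%, which is none within simulation error.

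**3. Other assumptions.**

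| Scenario | share lost |
|---|---|
| Falls depend purely on change (c = −b) | 0% |
| c = −0.5b | 20-25% |
| c = +0.5b (good baseline also protects) | 58-75% |
| c = b | 78-100% |
| c = 0, follow-up/baseline SD ratio 1.25 | 22% lost to 30% overstated |
| c = 0, SD ratio 0.8 | 60% to over 100% |

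The first four rows use ρ = 0.7 and r = 0 or 0.5; the last two use r = 0.5 and ρ = 0.5 to 0.9.

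**4. What this does to a hazard ratio (illustration).** Assume a direct HR of 0.70, a VT effect of 0.5 SD on the spatial score, and a log-rate slope of −0.35 per SD.

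- True mediated log HR: 0.5 × (−0.35) = −0.175. Total: ln 0.70 − 0.175 = −0.532. True mediated share: 0.175/0.532 = 33%.
- Change alone (half retained): −0.088. Share 16%; apparent direct HR exp(−0.532 + 0.088) = 0.64.
- Change plus MMSE at r = 0.6 (0.66 retained): −0.116. Share 22%; apparent direct HR 0.66.
- With the test's own baseline: share 33%, HR 0.70.

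**The case against.** **The covariate list is open.** It is introduced as including the named items, so the spatial baseline is left unnamed rather than ruled out. The models for cognitive change also follow the balance models, which adjust for baseline cognition. This stands: a reader might infer that the plan excludes the baseline, and the text does not say so. But the balance-type model describes the mediator, not falls, and the protocol does name baseline adjustment for the neighbouring change-score regression. The mediation sentence as published is therefore the weaker specification.

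**The mediator is worded as change.** If falls depend purely on change, nothing is lost. That is correct. It is, however, a special case: it needs baseline and follow-up scores to act on falls with equal and opposite slopes, so that patients with stably poor and stably good spatial skill fall at the same rate. The Background passage leans towards level but does not settle the matter.

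**A fixed loss is not supported.** A reader might infer that a third to a half of any true mediated effect disappears. The documents do not support that. The range needs three assumptions that they do not give, and step 3 shows that neither its size nor its direction is guaranteed.

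**The trial is small.** With 100 patients, under the step 4 truth (ρ = 0.7, r = 0.5), 1,500 simulated trials gave a mean mediated log HR of −0.11 (SD 0.10) with change plus MMSE, and −0.18 (SD 0.11) with the baseline added, against a true −0.175. Root mean squared error was 0.120 against 0.113. The bias is under one sampling SD and overall error hardly changes. This stands, and it limits the importance of the point.

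**Conclusion.** The point holds as a minor one. The cognition mediation step adjusts for change and names no baseline for the same spatial test, and baseline MMSE is only a partial substitute. Unless falls depend purely on change, the mediated effect is in general misstated. The loss is roughly 33-50% if falls depend on the follow-up level, the visit SDs are equal and the MMSE-spatial correlation is about 0 to 0.6. Elsewhere it can be nil, smaller, larger or reversed.

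The concern does not reach further. The balance mediator already has its baseline among the named covariates. Randomisation protects the total effect of VT on falls, and the stated power does not depend on this step. The analysis is exploratory, conditional on VT affecting cognition, and sits in a pilot of 100 whose primary aim is feasibility.

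**What to change.** In the cognition mediation model for falls, enter the baseline score of the same spatial test together with its change. This is equivalent to entering the follow-up score plus baseline: β1(M1 − M0) + β2M0 = β1M1 + (β2 − β1)M0, so the VT coefficient is identical. Keep that baseline in both falls models being compared, with and without the mediator, and fit both in the same patients, so that the shift in the VT hazard ratio reflects the mediator alone.

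The adjustment remains valid if falls depend only on change. It costs one sentence of analysis wording and one extra covariate in an exploratory model. No new data are needed, because the baseline spatial tests are already in the assessment schedule.
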